# Effectiveness and efficiency of assertive outreach for Schizophrenia in Germany: study protocol on a pragmatic quasi-experimental controlled trial

**DOI:** 10.1186/1471-244X-13-56

**Published:** 2013-02-15

**Keywords:** Home treatment, Psychiatry, Integrated care, Seriously mentally ill, Controlled trial

## Abstract

**Background:**

A model of assertive outreach (AO) in which office-based psychiatrists collaborate with ambulatory nursing services for providing intensive home-treatment is currently being implemented in rural areas of Lower Saxony, Germany. The costs of the model are reimbursed by some of the statutory health insurance companies active in Lower Saxony. Effectiveness and efficiency of this model for patients suffering from schizophrenia is evaluated in a pragmatic and prospective trial.

**Methods:**

Quasi-experimental controlled trial: patients receiving the intervention are all those receiving AO; controls are patients not eligible for AO based on their health insurance affiliation. Eligibility criteria: clinical diagnosis of schizophrenia (ICD-10 F.20), aged at least 18 years and being moderately to severely impaired in global functioning. Primary outcome: admission and days spent in psychiatric inpatient care; secondary outcomes: clinical and functional status; patient satisfaction with chronic care; health care costs. Follow-up time: 6 and 12 months.

**Discussion:**

The study faces many challenges typical to pragmatic trials such as the rejection of randomisation by service providers, the quality of treatment as usual (TAU) to which the intervention will be compared, and the impairment of the study subjects. Solutions of how to deal with these challenges are presented and discussed in detail.

**Trial registration:**

International Standard Randomised Controlled Trial Number:
http://ISRCTN34900108, German Clinical Trial Register:
http://DRKS00003351

## Background

The aim of modern mental health care is to enable severely mentally ill people to live integrated in the community and live as autonomously as possible. Modern mental health care does not only address psychiatric and other medical needs but also social and economic ones
[1,2]. It is, therefore, usually community oriented and is provided by different professions and services. However, the challenge that arises in modern mental health care is to provide continuity of care across services and service sectors
[3,4].

One possibility for improving continuity of care is to provide assertive outreach (AO) treatment. AO is an intensive and highly integrated approach for community mental health service delivery
[5]. AO usually includes the following elements: it is provided by multi-professional teams with a psychiatrist integrated into the team; AO takes over responsibility of health and social care; within AO regular and frequent home visits are provided
[6]. However, until now, the findings are controversial as to how far AO is better capable of improving patients’ clinical outcomes and to what extent it reduces the need for days spent in hospital compared to TAU
[7]. While older studies report significant effects of AO on patients’ wellbeing and days spent in hospital
[8,9], more recent studies fail to do so
[10,11].

In some countries, AO is being implemented nationwide and long-standing experience with AO does exist, such as in England and in the Netherlands. Other countries, such as Germany or Belgium, do not make AO available or rather, they are just in the process of implementing first AO-style models.

We will discuss a study protocol to evaluate the effectiveness and efficiency of a model of AO that is currently being implemented in rural areas of Lower Saxony, Germany. It is, thus, a protocol not of a trial but of a pragmatic study.

The German mental health care system is known for its fragmentation
[12]: there are separate budgets for in- and outpatient care. Most outpatient care is provided by office-based psychiatrists who operate as independent entrepreneurs. Also, ambulatory nursing services operate as independent entrepreneurs. The medical services that are provided by office-based psychiatrists and nursing services are reimbursed within the budget framework of the statutory health insurances. A further problem in mental health care relates to the scarcity of services in rural areas including office-based psychiatrists, outpatient departments linked to hospitals and social services specialised in serving the severely and chronically mentally ill. In this health system environment, possibilities for intensified outpatient care and cooperation across sectors are limited, and incentives to keep patients out of hospital are low. Thus, admitting patients to psychiatric inpatient care occurs rather quickly.

In this situation, office-based psychiatrists in the rural areas of Lower Saxony have set up collaboration with ambulatory nursing services in a framework of integrated care with the aim of providing a model of AO. The model provides intensive and integrated home treatment as an alternative to inpatient admission. The model is meant to serve the more severely ill, particularly persons suffering from schizophrenia. As core components, this model offers the following service elements (see also Table 
1):

•Outpatient care is provided by a multi-professional team. The team leader is an office-based psychiatrist.

•An outreach crisis service is available 24 hours, seven days a week. It is operated by ambulatory nursing services and is backed up by an office-based psychiatrist.

•Home -treatment is provided by nursing services and –if needed – by the psychiatrist.

•Case management is provided by the nursing services, coordinating all the care that the patient receives. Every patient is assigned to a specific nurse as her/his personal case manager. This nurse is replaced by other nurses only during times of her/his absence.

•Psychoeducation is offered regularly.

•Regular team conferences are held and attended by at least one representative of the nursing service and the psychiatrist.

•Care is provided on the basis of an evidence-informed treatment pathway. This treatment pathway was developed by psychiatrists participating in the intervention. The treatment pathway is based on the German national guideline for Schizophrenia. It considers regional conditions as well as prior experiences with integrated care concepts. The treatment-pathway defines precisely the interaction between the nursing service and the psychiatrist, but also when and how to involve other services such as social services (that have different cost-carriers and budgets than the medical services), rehabilitation services, or inpatient psychiatric care. The treatment pathway is binding for service providers that participate in the AO model. It provides also the basis for reimbursement of services within the AO-model. Thus for purposes of reimbursement service provision in relation to the treatment pathway is continuously monitored.

**Table 1 T1:** Comparison of service provision in “classic” assertive outreach, assertive outreach as implemented in Lower Saxony and treatment as usual (TAU) in mental health care in Lower Saxony and Germany

**Characteristics of service**	**“Classic ” assertive outreach according to DACT-Scale***	**Assertive outreach in Lower Saxony**	**Treatment as usual (TAU) in Lower Saxony/Germany**
Target population	Patients suffering Severe Mental Illness (SMI), high users of mental health services	Patients diagnosed with Schizophrenia	Patients diagnosed with any mental illness
Involved service providers	Multiprofessional: Psychiatrist, nurse and others	Office based psychiatrist in cooperation with specifically trained psychiatric nurse. Further professionals such as rehabilitation specialists are involved as needed. Their involvement is brokered by nurse (case management)	Office based psychiatrist and other services providers as needed (and if available). No standardized pathways for cooperation and exchange between service providers are implemented.
Home treatment	yes	yes	no
Case management	yes	yes	no
Interdisciplinary treatment conferences	yes	yes (usually involving psychiatrist and nurse), meeting once a week	no
Responsible for medical and social needs	yes	yes	no
24/7-service	yes	yes	no
Maximum frequency of contact	high	high	medium
duration of relation	longterm	longterm	longterm

*Dartmouth assertive community treatment scale
[13].

Office-based psychiatrists who are interested in offering this type of AO sign up with a management association (IVPNetworks GmbH). This management association takes care that psychiatrists perform according to the treatment guideline and it negotiates specific reimbursement schemes for the intervention with statutory health insurance companies. For the time being, the management association has contracted for AO with the Allgemeine Ortskrankenkasse (AOK) in Lower Saxony and with the Techniker Krankenkasse (TK).^a^ Among the patients served at one office based psychiatrist there can be some patients who are eligible for receiving AO, due to their health insurance affiliation, while others are not. Those eligible have to give written consent to be treated with AO. Currently, about 40 psychiatric practices in Lower Saxony have joined this management association. They provide AO in an area of 16,000 km^2^ and a population of 2 million (of which approximately one third is insured with the AOK or the TK).

The study presented in this protocol tests the following two main hypotheses:

I. Schizophrenic patients who are served by AO have significantly fewer admissions to psychiatric inpatient treatment than patients receiving TAU.

II. Schizophrenic patients who are served by AO have significantly fewer days of psychiatric inpatient treatment than patients receiving TAU.

In addition, further hypotheses are as follows:

III. Schizophrenic patients being served by AO do significantly better clinically and functionally than patients receiving TAU.

IV. Schizophrenic patients being served by AO are significantly more satisfied with the chronic care they receive than patients receiving TAU.

V. Treating schizophrenic patients by AO is more cost-effective than treating schizophrenic patients by TAU.

## Methods

The hypotheses named above will be tested in a prospective and controlled cohort study that is quasi-experimental due to the patient´s health insurance affiliation. The intervention of AO will be tested against TAU. Follow-up occurs after six and 12 months.

### Outcome and process parameters

The main outcome parameters are the number of admissions to inpatient treatment as well as the number of days spent there. Further outcome parameters include: psychiatric symptomatology, functional status, life satisfaction, adherence to medication, substance misuse, use of services, and satisfaction with chronic care. For details of the scales that will be used to assess these outcome parameters, please see Table 
2.

**Table 2 T2:** Instruments to assess and process

**Outcome parameter**	**Instrument**	**Hypotheses**	**To be filled out by**
**Psychosocial functioning (inclusion criteria)**	Global assessment of functioning [14]	II	Psychiatrist
**Psychopathology**	Brief Psychiatric Rating Scale (BPRS) [15]	II	Psychiatrist
			Patient
**Life satisfaction**	11 point scale from the German Socioeconomic Panel [16]	II	Patient
**Functional impairment**	WHO-Disability Assessment Scale (WHO-DAS II) [17]	II	Patient
**Substance misuse**	Alcohol Use und Drug Use Scale (AUS, DUS) [18]	II	Patient
**Medical adherence**	Medical Adherence Rating Scale (MARS) [19]	II	Patient
**Patient satisfaction with medical care**_**1**_	Patient Assessment of Chronic Care (PACIC) [20]	III	Patient
**Service use**^**1,2**^	Client Sociodemographic and Service Receipt Inventory (CSSRI) [21]	I+IV	Practice assistant

^1^ Scales assess outcome as well as process: receiving care in concordance with the chronic care model (PACIC) and use of services (CSSRI).

^2^ Is assessed at t0 and then every three months, in contrast to all other parameters that are assessed at t0 and six and 12 months later.

When selecting scales to measure outcome parameters, we did not only consider specificity and reliability of instruments but also practicability. We expect that the patients, who will be recruited into the study, will be quite impaired by the illness. Therefore, questionnaires need to be simple, easy to handle and not too time-consuming.

All parameters will be assessed at baseline (t0), after six months (t1), and after 12 months (t2) from all patients receiving the intervention and from all controls. The use of services however will be assessed every three months (5 times) from both groups.

The use of services will be assessed by means of the German version of the Client Sociodemographic and Service Receipt Inventory (CSSRI;
[22]). The CSSRI assesses the use of services retrospectively for the past three months by questioning the patient. The CSSRI reports not only the quantitative use of inpatient and outpatient medical and psychiatric services and medication, but also the use of other forms of public support. This includes the use of social services, such as housing, rehabilitation services, the patient’s income, including social benefits and other forms of state payments, as well as their vocational affiliation and number of days of sick leave. Thus, the CSSRI assesses not only the main outcome, i.e., days spent in psychiatric inpatient care, but also serves as documentation of the process of care across sectors and services for both the intervention and the control group. Finally, the information gathered by the CSSRI allows for calculating direct as well as indirect health care costs
[22,23].

Likewise, the German version of Patient Assessment of Chronic Care (PACIC;
[24]) that is used to measure patients´ satisfaction with chronic care, serves as an instrument to measure outcome as well as process. The PACIC assesses whether patients receive specific services and information – such as health education and shared decision making – that are proven to be significant in the care of chronic patients
[25]. Originally, the PACIC was developed for somatic medicine. However, it has been shown to be relevant also in the evaluation of care provided to mentally ill patients
[26].

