### Sample size

Previous studies performed in Leipzig, Germany, have shown a mean number of days spent in psychiatric inpatient care by schizophrenic patients of 47 (SD 83)
[27]. Further, studies estimated the mean decrease of inpatient days that can be expected from interventions to be 40%
[28]. According to Hedeker and colleagues (1999), a baseline sample size of 242 participants in each group would be required to detect a small effect size of 0.2 with a power of 0.80 at a two-tailed significance level of 0.05
[29].

Previous studies have shown that 20% of patients cannot be traced for follow-up or do not return questionnaires over a 12-month survey period
[27].We aim to reduce drop-out numbers by keeping records of patients' telephone contact details as well as secondary contact names and addresses at the practices of the attending psychiatrists. If patients fail to return for assessment to the attending practice, they are contacted by phone and asked whether they want to continue with the study. This way, we hope to keep the number of drop-outs at a rate of 10%. Thus, the total number of participants to be initially recruited will be 268 patients per group or 536 in total.

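### The protocol names both admissions and inpatient days as main outcomes, but elsewhere treats days as the only one, sizes the study on days alone, and numbers Table 2 for a different set of hypotheses

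*Protocol article*

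**What the plan says.** Three places name two outcomes:

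- Abstract, Methods: "Primary outcome: admission and days spent in psychiatric inpatient care", two quantities under a singular label.
- Background: "The study presented in this protocol tests the following two main hypotheses". Hypothesis I reads "Schizophrenic patients who are served by AO have significantly fewer admissions to psychiatric inpatient treatment than patients receiving TAU" and Hypothesis II reads "Schizophrenic patients who are served by AO have significantly fewer days of psychiatric inpatient treatment than patients receiving TAU". Hypotheses III (clinical and functional status), IV (satisfaction) and V (cost-effectiveness) follow as further hypotheses.
- Outcome and process parameters, opening: "The main outcome parameters are the number of admissions to inpatient treatment as well as the number of days spent there".

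Two places point to one outcome:

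- Outcome and process parameters, in the text on the service-receipt inventory (CSSRI): "the main outcome, i.e., days spent in psychiatric inpatient care".
- Sample size: the only clinical inputs are mean inpatient days of 47 (SD 83) and an expected 40% reduction in days. The only error rate in the document is stated here, a "two-tailed significance level of 0.05". No admission rate and no expected effect on admissions appear anywhere.

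The Statistical analysis section lists model families. It gives no order of testing, no split of alpha, and no statement on whether one or both main hypotheses must succeed.

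**The concern.** Naming the primary outcome is the protocol's own task, and a later analysis plan cannot remove a conflict among statements already published. As the text stands, a reader of the results could not tell whether an effect on admissions without an effect on days confirms the main hypothesis, confirms one of two, or is a secondary finding. Admissions is listed first among the main hypotheses, yet no figure shows that the study can detect a difference in it.

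If the choice is left until data are in hand, the more favourable of two related outcomes can be presented as the main one, and the nominal 5% no longer describes the chance of a false main claim.

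**Working it through.** **1. Table 2 against the Background hypotheses**

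| Instruments | Label in Table 2 | Hypothesis that fits in the Background |
|---|---|---|
| GAF, BPRS, life satisfaction, WHO-DAS II, AUS/DUS, MARS | II (there: inpatient days) | III |
| PACIC | III (there: clinical and functional status) | IV |
| CSSRI | I+IV (IV there: satisfaction) | I, II and V |

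Only the CSSRI's I agrees. All the labels fall into place under a four-item list: I inpatient use, II clinical status, III satisfaction, IV costs. That this is the list Table 2 follows is an inference, but it agrees with the singular main outcome in the CSSRI text and with sizing on days alone.

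**2. The plan's own sample size**

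Simple two-group formula, two-sided 0.05, power 0.80: n per group = 2(1.960 + 0.842)²/d².

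- d = 0.2 gives 393.
- d = 0.40 × 47/83 = 18.8/83 = 0.2265 gives 306.

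Neither is the printed 242. The article cites a longitudinal method but prints no within-patient correlation. With three time points and equal correlation ρ, n = 2(1.960 + 0.842)²(1 + 2ρ)/(3d²), and d = 0.2 returns 242 at ρ of about 0.425. So 242 cannot be called wrong, and the stated 80% is taken as given below. (A one-sided 5% calculation on 18.8/83 also returns 242; that is a separate matter to clarify.) Dropout: 242/0.9 = 268.9, against 268 printed, a negligible difference. Every route rests on days; none involves admissions.

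**3. Familywise error if both are tested at 0.05 and either counts**

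This rule is assumed; the document does not state it.

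- Independent tests, either direction: 1 − 0.95² = 9.75%.
- Independent tests, false claims in favour of AO only: 1 − 0.975² = 4.9%, against 2.5% for one test.
- Correlated tests, bivariate normal, correlation assumed:

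| Correlation | Either direction | In favour of AO only |
|---|---|---|
| 0.3 | 9.5% | 4.8% |
| 0.5 | 9.1% | 4.5% |
| 0.7 | 8.3% | 4.2% |
| 0.8 | 7.8% | 3.9% |
| 0.9 | 7.0% | 3.5% |

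Inpatient days arise from admissions, so a positive correlation is to be expected.

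**4. Cost of each remedy**

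- Fixed sequence, days then admissions: alpha for days stays at 0.05, and 242 (268 with dropout) per group is unchanged.
- Co-equal outcomes at 0.025 each: power per test at 242 = Φ(1.960 + 0.842 − 2.241) = about 71%, reading the stated 80% as the power at 0.05. To restore 80%, n rises by (2.241 + 0.842)²/(1.960 + 0.842)² = 1.211, so 242 becomes 294. Then 294/0.9 gives 327 per group, or 654 in total against the planned 536.
- For admissions no power can be computed, because no rate or effect is given. The 71% applies to admissions only if its standardised effect equals that assumed for days.

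**The case against.** The strongest reply is that the document never says each hypothesis is tested at 5%, nor that a win on either supports one overall claim. The hypotheses are worded as separate statements about admissions and days, and a multiplicity rule may sit in an analysis plan that is not shown. That stands: the error figures are conditional, and the absence of an adjustment rule is not itself the finding. It is also fair that the hypotheses are directional, so the 2.5% to 4.9% comparison is closer to a false claim for AO than 9.75% is.

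Three stronger readings are tempting, and the document does not support them:

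- A reader might infer from Table 2 that six clinical scales are tests of a main hypothesis. The Abstract lists clinical and functional status as secondary, the Background puts it under further hypotheses, and GAF is marked as an inclusion criterion. This is mislabelling, not a plan for six more main tests.
- A reader might infer that the cost hypothesis has no instrument. The CSSRI text says that its data allow direct and indirect costs to be calculated; only the label is missing.
- A reader might infer that reading both 6 and 12 months doubles the number of tests. Service use is collected every three months, five times, and the Statistical analysis section plans repeated-measures models that can use all waves together. Separate tests at the two times are not stated.

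Keeping both outcomes as main is also legitimate, since three places name both. It then needs a stated rule.

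**Conclusion.** The point holds as a contradiction within the published text: two main outcomes in the Abstract, Background and opening of the outcome section; one in the CSSRI text and in the sizing; and Table 2 numbered for another list. No analysis plan is needed to see this, and none could remove it.

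The inflation is a conditional consequence: about 7 to 9.5% two-sided for correlations of 0.3 to 0.9, with 9.75% as the independence limit, or about 3.5 to 4.9% against 2.5% for false claims in favour of AO. It assumes both tests at 0.05, either one sufficing, and each test holding its nominal size, which in a non-randomised comparison also depends on adequate control of baseline differences. The correlations are assumptions. The change should be made; it is inexpensive and does not call the study's feasibility into question.

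**What to change.** Reconcile the statements before outcomes are compared by group:

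- Name inpatient days over 0 to 12 months as the single primary outcome, as the sample size implies, and say so identically in the Abstract, the Background and the outcome section. Each CSSRI interview looks back three months, so the four follow-up interviews cover this period (4 × 3 = 12 months).
- Test admissions over 0 to 12 months as a confirmatory hypothesis only if days is significant at two-sided 5%.
- Relabel Table 2: clinical and functional scales to III, PACIC to IV, CSSRI to I, II and V.

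This leaves alpha and the 268 per group untouched. It is more than an edit, because it ranks what is now Hypothesis I behind Hypothesis II, and admissions could not be claimed as confirmatory if days is not significant.

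If the sponsor prefers two co-equal outcomes, state the alpha for each and restate the power (about 71% per test at 242 per group for a split at 0.025, taking the stated 80% as given), and supply an assumed admission rate and effect so that power for admissions can be shown.
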